### Participant recruitment

After receiving written approval from the school management teams, teachers at the specified levels (1st to 4th grade) will be invited to join the project. Each student and their parents or guardians will receive an information packet, which includes an informed consent form written in clear, understandable language. This form must be signed and returned to the research team for participation.

To promote inclusivity, every student in the involved classes will participate in video-guided active breaks. Nonetheless, data collection for the “Active Classes + School Climate and Mental Health” project evaluation will only encompass those students whose parents or guardians have provided consent. Additionally, the selection of participants will adhere to specific inclusion and exclusion criteria, guaranteeing their appropriateness for the research goals.

#### Inclusion criteria

• Students (both boys and girls) in primary education, from first to fourth grade, attend a public school in any of the three provinces of the Biobío region, who have received parental consent.• Schoolchildren who are in class for at least 38 h a week (6.5 h daily), with a schedule that includes at least two short breaks (15 min) each day.

#### Exclusion criteria

• Students diagnosed with spinal pathologies, vertigo, or uncontrolled hypertension.• Students with severe intellectual disabilities that prevent them from understanding and following the program instructions.• Students are already participating in another project that aims for similar outcomes.

Sampling will be non-probabilistic, convenient, and non-representative, involving voluntary subjects. Neither schools, teachers, nor children will receive any payment for participating in the project.

## Randomization of participating schools

After securing participation from schools, they will be randomly allocated to one of two groups through a sequence generated by the IBM SPSS software, ensuring concealed allocation. The groups are: 1) the Experimental Group (n = 3; 1 for each province), which will partake in a 12-week program of video-guided active breaks incorporating curricular content within the school classroom setting; and 2) the Control Group (n = 3; 1 for each province), which will receive the intervention after the conclusion of the initial data collection phase. This randomization allowed each province to have an experimental group and a control group. The random sequence will be kept confidential using sequentially numbered, opaque, sealed envelopes, managed by a researcher who will not interact with the schools or participants. Previous research with similar participant samples has identified significant differences in quality of life, motor skills, and academic performance, underscoring the potential impact of our intervention (Sánchez-López et al., 2019; Watson et al., 2017a).

## Guided video-active breaks program with curricular content

### Program development

The “Active Classes + School Climate and Mental Health” program was crafted following a comprehensive review by the research team on active breaks in the child school population (Robles-Campos et al., 2023). Based on the findings of this review, the optimal type and duration of intervention, frequency and intensity of the most effective exercises, and video-guided modalities with curricular content for active breaks will be established. Subsequently, a collaborative network was formed, involving researchers from education, sports science, social sciences, medicine, primary school teachers within the Chilean public school system, teams of educational leaders, parents, guardians, pedagogy students, and graduate students. The purpose was to create a team that systematically supports the development of various stages of the project from a multi- and interdisciplinary perspective.

### Development of an interactive web platform containing active breaks

An interactive web platform for active breaks, named “Active Classes” was created (https://clasesactivas-dev.usercode.cl/). The platform was designed and developed using modern technologies and cutting-edge frameworks to ensure an optimal user experience, ease of maintenance, and scalability. At the core of the web solution is Next. js, a React framework that enables the generation of static and server-side-rendered websites, optimizing performance and loading speed; crucial elements for enhancing the user experience. Regarding the backend, the platform relies on Node. js with Express, providing an efficient solution for building an API that powers the platform. This combination is widely recognized for its efficiency in handling real-time applications and its event-driven architecture, which facilitates the construction of scalable services. The choice of Node. js and Express for API development underscores the commitment to a service-based architecture that can efficiently handle asynchronous requests and support high workload. Data persistence is managed through a MySQL database chosen for its reliability, data integrity, and support for complex transactions. The use of SQL allows for structured data management with advanced query and analysis capabilities, which are essential for the efficient storage and retrieval of information on the platform. Overall, the platform’s architecture has been designed with a focus on modularity and separation of concerns, enhancing not only the maintainability and scalability of the system but also facilitating collaboration between development teams.

The platform has three access profiles: the administrator profile, used by the research team, allows for the general administration of the entire platform, including registering, creating, and deleting educational centres, accessing the use of educational centres, creating challenges, and analyzing data. The second profile is administered by the school climate coordinator, designed for a professional from each educational centre. It enables to register and unregister teachers from their centre and monitor challenges and progress in each course and level. Finally, the teacher profile allows them to create and implement active breaks in the classroom and monitor the progress of their challenges.

The platform offers an exercise bank used in active breaks, comprising coordination exercises (bilateral body coordination) and basic motor skills (balance, jumps, movement), previously used (Sánchez-Oliva et al., 2022). These exercises are performed on the platform by two animated characters (Ayun, which means love in the Mapudungun language of the indigenous Mapuche people, and Paz). They aim to encourage the identification and adherence of participating students. Both animated characters were developed for this project, and as the main goal is to contribute to mental health and the school climate, the exercises are performed in pairs to promote cooperative work (see Figure 2). Additionally, based on evidence from interventions in the school context, the “active classes” platform incorporated a gender perspective, recognizing that boys and girls have the same learning and development potential and the same opportunities to enjoy technological development equally. It also proposes cooperative workspaces through the execution of exercises in pairs and inclusion through an educational resource of exercises adapted to conditions of reduced mobility hosted on the platform, and the English language to strengthen the L2. Thus, the “Active Classes” platform has an initial bank of active breaks, but additionally, each classroom teacher will have a personalized user account, allowing them to apply and design their own Active Breaks.

**FIGURE 2 F2:**
[figure not shown]
Interactive Web Platform for Active Breaks - “Active classes”. **(A)** Loggin page, **(B)** Initial bank of active breaks, **(C)** Runing active breaks.

### Program “active classes” and specification of each active break

The “Active Classes” program was designed for students in 1st to 4th grade, encompassing students from 48 classes across 6 schools in the Biobío province, Chile. The program involves the implementation of video-guided active breaks with curricular content from any elective subject. These breaks last between 5 and 10 min, feature a moderate to vigorous intensity, occur twice a day every day of the week, and span a duration of 12 weeks. The activities are drawn from the “Active Classes” platform specifically developed for program implementation.

The schedule for implementing active breaks is flexible and is determined by each teacher, considering variations in school and class schedules. However, a stipulation is in place to ensure that active breaks are not conducted during physical education classes at the beginning or end of the class but as a disruption within the class period. The priority order for subject areas during active breaks is math, language, social sciences, natural sciences, and English. Each active break consists of three distinct phases or moments: the “welcome and preparation,” the “central content,” and the “closure and cool-down (see Table 1).

**TABLE 1 T1:** Active Breaks in the “Active Classes + School Climate and Mental Health” intervention program.

Components of the active break	Duration	Description	References image of the “active classes” platform
*Welcome and preparation*	1 min	Mainly motivational phrases, self-esteem boosters, teamwork encouragements delivered by the characters of the ‘Active Classes’ platform, to motivate students to engage in active breaks	[figure not shown]
*Central Content*	4 min	The central content is mainly the application of active breaks with curricular content through interval exercise. Thus, after presenting a curricular content question and the exercises associated with each answer choice, the characters from the “Active Classes” platform guides students in performing the exercise associated with the correct answer for 20 s at a moderate to vigorous intensity, followed by 20 s of complete rest. The students have to choose between two exercises depending on which one they think is the correct answer. The curricular content covers any subject in the school curriculum, and the exercises includes motor and coordination activities performed in pairs cooperatively (e.g., partner burpees)	[figure not shown]
*Cool Down*	1 min	Simultaneously, the characters from the “Active Classes” platform guides students in performing breathing control exercises while providing feedback messages for active participation. After these exercises, students resume their lesson	[figure not shown]

### Teacher sensitization and familiarization sessions prior to implementation

Before implementing the program, all teachers at the levels to be intervened will participate in training with the aim of providing the “Active Classes + School Climate and Mental Health” manual for teachers. The training session is designed to inspire and equip teachers with the necessary skills and knowledge to implement the program through an interactive platform hosting guided video-active breaks. It will take place in schools and will be conducted by a physical education teacher with extensive experience in implementing physical activity interventions, who is part of the research team that developed the intervention program and interactive platform “Active Classes.” At the end of the training, teachers will receive certification and printed and digital materials from the project. This included didactic material with adapted exercises for the implementation of active breaks in students with reduced mobility and/or disabilities. All these materials will be open access for use.

## Variables and instruments

Characterization variables of schoolchildren reported by the parents were measured through a auto-fill questionnaire only once before the intervention (sociodemographic variables such as birthdate, sex, nationality, place of residence, school, course, class schedule, participation in school integration program and sports activities, type of travel to and from school, usual clothes to wear at school, absence, previous pathologies, vision and hearing were measured with a self-developed instrument. Additionally, consumption, habits and practices of feeding was measured with a validated instrument in Chilean schoolchildren (Vio del Rio, 2015), which will be included as covariates to fit the proposed models in the mixed model analysis. Subsequently, the following variables will be measured in all participants before and after the intervention.

### Primary outcome variables

#### Mental health

The mental health of students will be assessed through self-esteem and socioemotional wellbeing. Self-esteem will be evaluated using a School Self-Esteem Test. This scale, developed and validated in Chile by (Marchant et al., 2001), awards one point for each positive response and zero for each negative response. The raw score sum is transformed into a T score according to age norms, categorizing students as follows: normal self-esteem, ≥40 points; low self-esteem, 30–39 points; and very low self-esteem, ≤29 points. The internal consistency level achieved in this questionnaire with the current sample achieved a Cronbach’s alpha of 0.81. This variable will be assessed in students of 3rd and 4th grade during the study.

Two instruments will be used to assess socioemotional wellbeing. A) Self-report of socioemotional wellbeing. This scale, developed and validated in Chile by Edwards et al. (2022), will be evaluated in students of 1^st^ and 2^nd^ grade during the study. The questionnaire has adequate psychometric properties in terms of test-retest reliability for different socioeconomic levels (correlations range from 0.761 to 0.949) and internal consistency for the entire test (Cronbach’s Alpha of 0.82). B) The Integral Learning Diagnosis. This instrument, implemented by the Education Quality Agency, is applied three times per year. There is an initial evaluation at the beginning of the year, an intermediate evaluation, and a final evaluation. For this study, the evaluative socioemotional activity test (1st, 2nd, and 3rd-grade students) and the Socioemotional Questionnaire (4th-grade students) were used at three points: the beginning, middle, and end of the school year. The evaluative socioemotional activity is a space for expression and dialogue that assesses the socioemotional skills of girls and boys according to their level, which was evaluated in previous application periods: self-awareness, awareness of others, inclusion, collaboration and communication, empathy, pro-sociality, self-regulation, and democratic commitment. The socioemotional questionnaire collects information about students’ perceptions in two areas: socioemotional learning - both in themselves and regarding the school’s management - and key aspects of comprehensive training (Agencia Nacional de Educación, 2022).

#### School climate

The Social Climate Scale developed by Aron et al. (2012) will be used. The social climate scale includes 82 items with a four-level Likert-type response format (ranging from all to none). For this study, only three subscales will be considered: teachers (30 items, e.g., “they are reliable,” “they notice when someone has problems”; Cronbach’s alpha reliability index of .84), peers (15 items, e.g., “My classmates laugh at me,” “I know how to share”; Cronbach’s alpha of .81), and the school context (ten items, e.g., “My school is clean and well-organized,” “I have enough working materials in my classroom”; Cronbach’s alpha of .68) (Aron et al., 2012). This variable will be assessed in students of 3^rd^ and 4^th^ grade during the study. This instrument is completed by the students.

### Secondary outcome variables

#### Health-related physical fitness

This will be assessed using the Alpha Fitness Test battery protocol, which includes measurements of cardiorespiratory, musculoskeletal, and motor condition (Ruiz et al., 2011). Cardiorespiratory condition will be assessed using the 20 m Shuttle Run Test (20 m SRT), also known as the Course Navette. The test involves running back and forth on a 20 m track marked between two lines separated for as long as possible. The pace is set by audio signals, starting at 8.5 km/h and increasing at 0.5 km/h intervals every 1 min. The test ends when the student stops due to fatigue or fails to reach the final line simultaneously with the beep on two consecutive occasions. The performance of the student during the test will be recorded using the number of 20 m laps (1 lap = 20 m) and the total time (s). Musculoskeletal fitness will be assessed using the Standing Broad Jump (SBJ) and the grip strength of the dominant hand. The SBJ test will be used as an indicator of lower-limb strength. It involves jumping the farthest distance possible from a standing position, with both feet and swinging both arms. The distance is measured from the take-offline to the point where the back of the heel closest to the take-offline touches the ground. The grip strength of the dominant hand will be used as an indicator of upper limb strength (A hand dynamometer with adjustable grip (TKK 5101 Grip D; Takey, Tokio Japan). The elbow must be in full extension and avoiding contacting with any other part of the body with the dynamometer, except the hand being measured. The students will be asked to squeeze the dynamometer twice with each hand. The maximal duration of the test is 3–5 s. To control fatigue effects, attempts were alternated between hands with approximately 2 min of rest between each attempt for each hand. The best measurement for each of the two attempts will be recorded. Motor condition will be assessed using the 4 × 10 m Shuttle Run Test, which involves running back and forth between two lines separated by 10m, taking three sponges alternately as quickly as possible. The total distance covered is 40 m. This variable was evaluated by blinded evaluators who were previously trained for the test, and were conducted with the same instruments in all schools.

#### Basic motor competencies

The MOBAK Test Battery will be used to evaluate basic Motor Competencies (Cárcamo Oyarzún and Herrmann, 2020; Herrmann et al., 2015). This battery assesses the status and development of basic motor competencies during the early years of schooling. It assesses motor competencies “Body Control” with four tasks (balancing, rolling, jumping, running) and “Object Control” with four additional tasks (throwing, catching, dribbling a ball with the hand, dribbling a ball with the foot). The difficulty and complexity of the MOBAK Test tasks have been established according to the age of the children. MOBAK one to two will be used for students in 1st and 2nd grade, and MOBAK 3-4 for students in 3rd and 4th grade during the study. All tests were conducted in the physical education gyms of the participating schools during scheduled physical education classes. The tests will be administered to small groups of six or fewer participants at each test station at any time. In addition, to address fatigue or sequencing of tests as potential sources of measurement error, all participants had a minimum rest period of–3–5 min between each test. This variable was evaluated by blinded evaluators who were previously trained for the test.

#### Physical activity, sedentary behavior and sleep

The Questionnaire for the Measurement of Physical Activity and Sedentary Behavior is designed to be filled out by parents or caregivers (Camargo et al., 2015). It aims to gather information on three specific behaviors - physical activity, sedentary behavior, and sleep - for each day of the week following the school day. For physical activity, the questionnaire covers various aspects including walking to the Child Development Institute (CDI), participation in organized sports, and eight different types of active play. When it comes to sedentary behaviors, it focuses on two main areas: time spent reading and engaging in screen-related activities (such as watching television, using computers, and playing on game consoles). Sleep duration in the questionnaire encompasses both naps and overnight sleep.

Responses for each activity are to be marked with a “yes” or “no”. For any activity marked “yes”, parents or caregivers are asked to specify the duration in minutes that the child spent on that activity for each day of the week. This allows for a detailed breakdown of the frequency and duration of each type of activity over the 7 days, with a clear distinction between weekdays and weekend days (total time spent during Saturday and Sunday).

In terms of reliability, the instrument has demonstrated a Cronbach’s alpha coefficient of .64 for records of physical activity time and ranged between .34 and .23 for sedentary behaviors, indicating varying levels of consistency in these measurements (Camargo et al., 2015). This data is provided by the parents or guardians of the children taking part in the study.

#### Academic performance

The academic performance of the students will be measured using Integral Learning Diagnosis. For this study, only the reading test (2nd, 3rd, and 4th grades) and mathematics test (3rd and 4th grades) were used, measured at the beginning and end of the school year. The reading and mathematics tests measure acquired learning as defined by the curriculum update established for 2023–2025. The reading test assesses the ability to locate, interpret, relate, and reflect. For mathematics, thematic axes are evaluated according to the level (National Education Agency, 2022).

The assessments will be conducted by a trained teacher, supervised by the research team. Teachers will not know the assignment to either study group, thus ensuring an impartial procedure. In addition, assessments will be conducted in person and in locations with optimal privacy, temperature, and humidity conditions (Table 2). Furthermore, parents will complete a sociodemographic form recording the sociodemographic, health, habits, and dietary characteristics of the students (Table 2).

**TABLE 2 T2:** Variables, instruments and administration characteristics.

Category	Variables	Instruments	Administered by	Performed By	Time of assessment	
					Baseline Assessment	Final assessment
Sociodemographic	Health, habits, and dietary consumption, characteristics of the students and parents	Sociodemographic Information Form	Autofill	Parents or guardians of students in 1st, 2nd, 3rd, and 4th grade	x	
School climate	School social climate	School climate scale (ECLIS)	E. C. Teacher trained by the research team	Students in 3rd and 4th grade	x	x
Mental health	School self-esteem	School Self-Esteem Test (SSET)	Autofill	Teachers of students in 1st, 2nd, 3rd, and 4th grade	x	x
	Socioemotional wellbeing	Self-report of socioemotional wellbeing	Autofill	Teachers of students in 1st and 2nd grade	x	x
	Socioemotional wellbeing	Comprehensive Learning Diagnosis (DIA) (Evaluative socioemotional activity)	Autofill	Teachers of students in 1st, 2nd, and 3rd grade	x	x
		Comprehensive Learning Diagnoses (DIA) (Socioemotional questionnaire)		Teachers of students in 4th grade	x	x
School performance	Mathematical performance	Comprehensive Learning Diagnosis (DIA) (mathematics test)	Autofill	Teachers of students in 1st, 2nd, and 3rd grade	x	x
	Reading performance	Comprehensive Learning Diagnosis (DIA) (reading test)		Teachers of students in 2nd, 3rd, and 4th grade	x	x
Physical health	Cardiorespiratory condition	ALPHA-Fitness battery (20-m shuttle run test)	E. C. Teacher trained by the research team	Students in 1st, 2nd, 3rd, and 4th grade	x	x
	Musculoskeletal condition	ALPHA-Fitness battery (handgrip strength and standing long jump)			x	x
	Motor condition	ALPHA-Fitness battery (4 × 10-m shuttle run test)			x	x
	Motor competence	MOBAK 1–2	E. C. Teacher trained by the research team	Students in 1st and 2nd grade		
		MOBAK 3–4		Students in 3rd and 4th grade	x	x
	Physical activity	Questionnaire for the Measurement of Physical Activity and Sedentary Behavior (C-MAFYCS)	Autofill	Parents or guardians of students in 1st, 2nd, 3rd, and 4th grade	x	x
	Sedentary behavior				x	x

Note. E.C., educational center.

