## Methodology

### Study design

This study adopts a multicenter, cluster, randomized, double-blind (evaluator and data analyst blind to each other) controlled trial design, with two arms, registered on ClinicalTrials.gov under the identifier NCT06423404, as of 20 March 2024. Six public educational centers in the Biobío region, Chile, were invited to participate (two from Biobío province, two from Arauco province, and two from Concepción province). The study followed the CONSORT guidelines for clinical trials (Butcher et al., 2022), reporting on social and psychological interventions (Montgomery et al., 2018), and the SPIRIT guidelines for protocol studies (Chan et al., 2013).

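### The article says assessing teachers do not know the allocation and calls the trial double-blind, but whole-school allocation and teacher-run breaks rule this out at the final assessment, and Table 2 contradicts the text on who responds and who assesses

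*Protocol article*

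**What the plan says.** The closing paragraph of Academic performance introduces Table 2, which covers every instrument in the trial. It says "The assessments will be conducted by a trained teacher, supervised by the research team", and then: "Teachers will not know the assignment to either study group, thus ensuring an impartial procedure". Study design labels the trial "double-blind (evaluator and data analyst blind to each other".

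Other sections describe what teachers do. Before implementation, "all teachers at the levels to be intervened will participate in training", and they leave with a manual and certification. The platform's teacher profile is for creating and running breaks and following the class's progress. On timing, "The schedule for implementing active breaks is flexible and is determined by each teacher". The process evaluation adds that the classroom teacher chooses the breaks.

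In Table 2 the self-esteem row gives the performer as "Teachers of students in 1st, 2nd, 3rd, and 4th grade". The other three mental-health rows likewise name teachers of the relevant grades. The school climate row gives the administrator as "E. C. Teacher trained by the research team", with pupils of 3rd and 4th grade responding. The table note expands E.C. as educational center.

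**The concern.** The primary outcomes, mental health and school climate, are subjective. With such measures, whoever responds, scores or supervises can be influenced by knowing the arm. A stated blinding of assessors tells readers that this risk has been dealt with. If the statement is untrue, the trial report would carry an assurance about its primary outcomes that the design cannot give. The limitations in the Discussion would not correct it, because they mention only the lack of a placebo-type comparison group.

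A second problem is tied to the first. If the text and Table 2 disagree on whether the pupil or the teacher responds, the primary measurement itself is not fixed. Pupil report and teacher report of the same construct are different measurements, with different exposure to bias.

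**Working it through.** No formula applies, and the article gives no figure to reproduce. The check sets the sections side by side.

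**1. Can teachers be unaware of the arm?**
- Randomization of participating schools: the school is the unit, three per arm and one per arm in each province. Control schools receive the programme after data collection.
- Teacher sensitization, platform development, programme specification and process evaluation: intervention teachers are trained in, schedule, choose and run the breaks, twice a day for 12 weeks.
- A teacher who delivers the programme knows the arm. A colleague in the same school, where all 1st to 4th grade classes take part, can readily learn it. Blinding could hold at baseline if that assessment came before allocation, which the article does not say. It cannot hold at the final assessment.

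**2. Does this reach the primary outcomes?** Table 2, primary rows:

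| Row | Administered by | Performed by |
|---|---|---|
| School climate scale | Teacher of the educational center | Pupils, grades 3–4 |
| Self-esteem test | Autofill | Teachers, grades 1–4 |
| Wellbeing self-report | Autofill | Teachers, grades 1–2 |
| DIA socioemotional activity | Autofill | Teachers, grades 1–3 |
| DIA socioemotional questionnaire | Not separately stated | Teachers, grade 4 |

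Four mental-health rows plus one climate row make 4 + 1 = 5, and a school teacher appears in all five. In the climate scale, 30 of the 30 + 15 + 10 = 55 items used form the teacher subscale, so pupils answer largely about teachers while a teacher of the school administers. That count describes content and does not measure bias.

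**3. Does Table 2 agree with the text?**
- Wellbeing: the Mental health section names the instrument "Self-report of socioemotional wellbeing" and evaluates it in pupils of grades 1–2. Table 2 has their teachers perform it.
- Self-esteem: the Mental health section assesses pupils of grades 3–4. Table 2 lists teachers of grades 1–4.
- Physical tests: the fitness and motor competence sections say evaluators were blinded. Table 2 names a teacher of the educational center.
- Mathematics: the Academic performance text uses grades 3–4. Table 2 lists teachers of grades 1–3.

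**4. Does the label help?** Evaluator and analyst being blind to each other is not the same as either being blind to allocation. If the phrase was meant to say that both are blind to allocation, the evaluator half still fails wherever the evaluator is a teacher of an allocated school. The analyst half could be true, but the article does not establish it.

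**The case against.** **The assessor may not be the person who delivers the breaks.** A reader might infer that the class teachers who run the breaks also assess every outcome. The documents do not go that far. The text says only that the assessor is a trained teacher, and for the climate scale and physical tests Table 2 says only that the teacher belongs to the educational center. Grade teachers are named explicitly only in the mental-health rows. This part of the objection stands. It does not rescue the blinding claim, because another teacher in a school allocated as a whole is not credibly blind.

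**The performer column may be mislabelled.** A reader might infer that teachers rate the pupils' mental health. The same column also lists teachers for the mathematics and reading tests, so it cannot safely be taken to name the respondent. A table error is at least as plausible as teacher rating. This stands too, and it is a reason to correct the table. If pupils respond, they are also aware of the intervention.

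**Size and direction of bias.** A reader might want to put a figure in SD units on the bias, or say that it acts in one arm only. Nothing in the documents supports a figure. Assessments take place in both arms, control schools are promised the programme later, and all schools are chosen partly for enthusiasm. Bias towards benefit is plausible but not shown.

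**Such trials cannot blind teachers or pupils.** Agreed, and nobody need try. The fault lies in claiming blinding that is absent. Nor does the article's condensed form explain it, since this is a statement that the article's own text refutes.

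**Conclusion.** The point holds. The article claims a property that its own design excludes at the final assessment: teachers unaware of allocation, under a double-blind label. The claim covers all five primary-outcome rows of Table 2 and, through the conflict over blinded evaluators, the physical tests among the secondary outcomes. Table 2 also leaves the respondent for the wellbeing self-report and the grades for self-esteem in contradiction with the text.

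The conclusion rests on whole-school allocation and on teachers delivering the programme, both stated in the article. One modest inference is added: that a non-delivering teacher in an allocated school would learn the arm. It does not depend on who the climate-scale administrator turns out to be, on how the performer column is read, or on any assumed size of bias. It should be corrected before results are reported, because it changes how far an effect on self-reported or teacher-reported outcomes can be attributed to the breaks.

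**What to change.** - Delete the sentence on teacher blinding and the double-blind label.
- State that pupils and teachers are not blinded.
- Claim blinding to allocation only for roles where it is actually in place. The data analyst is one candidate. The physical-test evaluators qualify only if they are not teachers of the school.
- Correct Table 2 so that respondent, administrator and grades for each instrument agree with the Mental health, School climate, fitness and motor competence sections, with pupils as respondents for the wellbeing self-report. Correct the mathematics grades at the same time.
- Label any instrument that a teacher does complete as unblinded.
- Add unblinded, subjective primary outcomes to the limitations, and carry that into the interpretation of any effect.

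Handing administration to the research team would not by itself restore blinding. The team built the platform and trains the teachers, and the article does not show that its members are masked.

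The cost is a few sentences and one corrected table. It requires the investigators to confirm, for each instrument, who responds, who administers and who is masked. No change to sample size or analysis is needed.
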